## Abstract

**Background:**

For obstructive colon cancer, many studies have been conducted on the use of self-expandable metallic stents (SEMS) as a bridge to surgery (BTS). However, there are currently no available prospective data on the impact of bridging period and there is a lack of research on the effects of neoadjuvant chemotherapy during the bridging period.

**Objectives:**

Patients who undergo successful SEMS placement for obstructive left-sided colon adenocarcinoma without metastases will be eligible for this study.

**Design:**

This study is a multicenter, non-inferiority, randomized (1:1), open-label, controlled trial.

**Methods & analysis:**

The patients assigned to the control group will undergo curative surgery within two weeks after successful SEMS placement. The patients assigned to the experimental group will undergo three cycles of neoadjuvant FOLFOX chemotherapy within two weeks after successful SEMS placement. Curative surgery will be performed within four weeks of the last administration of neoadjuvant FOLFOX. Circulating tumor DNA (ctDNA) will be collected at specific time points.

**Discussion:**

The optimal time interval for SEMS placement as a BTS can significantly impact long-term oncologic outcomes. In this study, our goal is to identify the optimal time interval for SEMS placement as a BTS. Recently, there has been interest in applying neoadjuvant chemotherapy for locally advanced colon cancer. In the context of early treatment for tumor dissemination following SEMS placement, neoadjuvant chemotherapy may be beneficial for delayed surgery after SEMS placement as a BTS. The results of this trial will be an important reference for the application of neoadjuvant chemotherapy in locally advanced colon cancer. Additionally, researchers will investigate whether ctDNA can serve as a reliable indicator to guide decisions about the timing and type of subsequent treatment. Based on the results of this trial, a patient-tailored treatment strategy can be developed for obstructive colon cancer.

**Registration:**

This study is registered on ClinicalTrials.gov Identifier: NCT04889820, registered on May 17, 2021 in clinicaltrials.gov; Protocol ID: XC21MIDI0004.

**Supplementary Information:**

The online version contains supplementary material available at 10.1186/s12885-025-13588-0.

## Introduction

It is known that around 30–40% of colorectal cancer require emergency surgery. Colonic obstruction accounts for 80% of emergency treatment cases, while colon perforation accounts for the remaining 20% [1–3]. Patients with colorectal cancer who require emergency surgery have higher rates of postoperative complications, mortality, and ostomy formation compared to those who do not require emergency surgery [4, 5]. Patients who undergo emergency surgery tend to have worse long-term survival rates in terms of oncological outcomes [6]. Despite recent efforts to actively screen for colorectal cancer, some studies have reported that the proportion of cases resulting in obstruction or perforation requiring emergency surgery has remained unchanged [7, 8]. However, research on treatments aimed at reducing postoperative complications and improving long-term survival for patients with symptomatic colorectal cancer who require emergency surgery is still insufficient.

Emergency surgery cannot be avoided when colorectal cancer causes perforation of the colon. Obstructive colorectal cancer has traditionally been treated with emergency surgery, which involves resecting the affected part of the colon and creating a stoma. With the advancements in endoscopic equipment and technology, it has become possible to insert endoscopic stents, such as self-expandable metallic stents (SEMS), in patients with obstructive colon cancer. Numerous studies have been conducted on the use of SEMS as a bridge to surgery (BTS), which involves performing surgery after achieving sufficient decompression and bowel lavage through the placement of SEMS [9]. These studies have shown that a BTS can reduce postoperative complications, stoma formation, and postoperative mortality in select cases [9]. Currently, these studies recommend the use of SEMS to improve short-term postoperative outcomes. However, the long-term oncological outcomes of SEMs as a BTS have not yet been established.

After SEMS placement, the primary objectives of BTS may include performing oncologic surgery on patients with obstructive colon cancer who are in a more stable or improved physical condition, conducting one-stage surgery to avoid the need for a diverting stoma, and reducing postoperative morbidity. To achieve the dual goals of improved perioperative and oncologic outcomes, some studies have focused on optimizing the interval between the placement of SEMS and elective surgery [10, 11]. The current guideline from the European Society of Gastrointestinal Endoscopy (ESGE) suggests a time interval of approximately two weeks before resection when colonic stenting is used as a bridge to elective surgery for patients with curable left-sided colon cancer [12]. However, there are currently no available prospective comparative data on the impact of this period on surgery, complications, or overall and disease-free survival. Furthermore, there is a lack of significant research on the effects of neoadjuvant chemotherapy during the bridging period.

In this study, our objective is to determine the optimal time interval for curative resection after successful placement of SEMS for obstructive colon cancer. Additionally, our aim is to investigate whether neoadjuvant chemotherapy, followed by curative resection, can improve short-term perioperative outcomes and long-term oncological outcomes.

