### The control group

The patients assigned to the control group will undergo curative surgery within two weeks after successful SEMS placement. After their recovery from surgery, they will receive adjuvant FOLFOX chemotherapy within four weeks. Adjuvant FOLFOX chemotherapy will be administered every two weeks for six months, totaling 12 cycles.

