### The experimental group

The patients assigned to the experimental group will undergo neoadjuvant FOLFOX chemotherapy within two weeks after successful SEMS placement. After three cycles of neoadjuvant FOLFOX chemotherapy, the patient will undergo a follow-up study, including a serum CEA, abdomen and pelvic CT, and either a chest PA or chest CT, to determine the status of the tumor. If no metastatic lesions are found in these assessments, curative surgery will be performed within four weeks of the last administration of FOLFOX. After their recovery from surgery, they will receive adjuvant FOLFOX chemotherapy within four weeks. Adjuvant FOLFOX chemotherapy will be administered every two weeks for approximately four months, totaling nine cycles. The experimental group will receive a total of 12 cycles of perioperative FOLFOX chemotherapy. The flowchart of the study is presented in Fig. 1.

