The optimal time interval for SEMS placement as a BTS can significantly impact long-term oncologic outcomes. After SEMS placement, the primary objectives of BTS may include performing oncologic surgery on patients with obstructive colon cancer in a more stable or improved physical condition, conducting one-stage surgery to avoid the need for a diverting stoma, and reducing postoperative morbidity [10, 11]. To achieve this, it is necessary to establish the optimal time interval between SEMS placement and elective surgery. However, there is limited data available regarding the optimal time interval. One strategy could be to schedule elective surgery as soon as possible after SEMS placement to reduce the risk of tumor dissemination and alteration of pathological findings. This approach can also minimize the interaction between the tumor and the prosthesis, such as a stent. A retrospective study conducted in Japan with 47 patients who underwent BTS after SEMS placement demonstrated that the interval of 15 days between SEMS placement and surgery was the only independent risk factor for postoperative complications. They recommended an interval of more than 15 days to minimize postoperative complications [17]. In an Italian study, the authors found that various time thresholds did not have a correlation with the occurrence of postoperative morbidity [18]. However, the ROC curve for postoperative morbidity indicated that waiting for at least six days could be appropriate surgical timing. A multicenter retrospective study conducted in Denmark revealed that the risk of recurrence significantly increased in the group with a time interval of more than 18 days [19]. By using an “intention-to-treat” model that included patients who underwent emergency surgery due to complications from stent placement, the researchers found that the risk of recurrence was significantly higher in the group with a time interval of more than 18 days. Our multicenter retrospective study found that the time interval between SEMS placement and elective surgery did not significantly affect perioperative short-term outcomes [10]. However, early elective surgery within 7 days, or at least within 14 days, after SEMS placement may reduce the oncologic risk of BTS. In this study, we aim to analyze the short-term perioperative outcomes and long-term oncologic outcomes based on the time interval between SEMS placement and elective surgery. Our goal is to identify the optimal time interval for SEMS placement as a BTS.

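### The stated objective, the optimal SEMS-to-surgery interval, cannot be answered by the randomised comparison, because interval and neoadjuvant chemotherapy change together between the arms

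*Protocol article*

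**What the plan says.** The Introduction puts the interval first: "our objective is to determine the optimal time interval for curative resection after successful placement of SEMS for obstructive colon cancer". Chemotherapy follows as a further aim: "Additionally, our aim is to investigate whether neoadjuvant chemotherapy, followed by curative resection, can improve short-term perioperative outcomes and long-term oncological outcomes". The Abstract, under Discussion, says that "our goal is to identify the optimal time interval for SEMS placement as a BTS". The main Discussion says "we aim to analyze the short-term perioperative outcomes and long-term oncologic outcomes based on the time interval between SEMS placement and elective surgery" and then restates the same goal.

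The arms are described as follows:

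- Control: "The patients assigned to the control group will undergo curative surgery within two weeks after successful SEMS placement". This arm has no neoadjuvant chemotherapy and is planned to have 12 adjuvant cycles.
- Experimental: patients "will undergo neoadjuvant FOLFOX chemotherapy within two weeks after successful SEMS placement". Then: "After three cycles of neoadjuvant FOLFOX chemotherapy, the patient will undergo a follow-up study". Surgery follows within four weeks of the last administration if no metastases are found, and nine adjuvant cycles complete a total of 12.

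Allocation is 1:1 with 204 patients (Sample size and randomization). The statistical analysis section specifies one test of the primary endpoint. It is an unadjusted Cox comparison of the arms, with non-inferiority declared if the upper limit of the one-sided 95% interval for the hazard ratio is below 2.29 in both the intention-to-treat and per-protocol analyses. Survival is counted from SEMS placement in both arms (Endpoint).

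**The concern.** The objective asks about one factor, the time from stent to resection. The randomisation changes two factors at once: that time, and whether three of the 12 chemotherapy cycles come before surgery. No arm has delayed surgery without neoadjuvant chemotherapy, no arm has early surgery with it, and no patient is randomised to an interval alone.

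What is at stake is the conclusion, not the conduct of the trial. The Introduction says that no prospective comparative data exist on the bridging interval, so readers may take this trial as that evidence. A non-inferior result could then be quoted as showing that delay itself is safe, which the trial does not test.

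**Working it through.** **1. The plan's own power figure.** Inputs are from Sample size and randomization: reference hazard 0.0446 per year, true hazard ratio 1.00, margin 2.29, 204 patients, uniform accrual over 3 of 6 years, dropout 0.01 (taken as 1% per year in each arm). One-sided alpha of 0.05 is from the statistical analysis section.

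- The inputs agree with each other: −ln(0.80)/5 = 0.0446 and ln(0.60)/ln(0.80) = 2.289.
- Expected deaths over both arms: 36.15.
- Power = Φ(√(D/4) × ln 2.29 − 1.645) = Φ(3.006 × 0.8286 − 1.645) = Φ(0.846) = 80.1%.

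The figure reproduces. It is the power to compare two strategies; nothing in it refers to the interval as such.

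**2. The SEMS-to-surgery window in each arm.** Inputs are from The control group, The experimental group and Chemotherapy (two-week cycles).

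| | Control | Experimental |
|---|---|---|
| Start of neoadjuvant FOLFOX | none | day 0 to 14 |
| First to third administration | none | 2 × 14 = 28 days |
| Last administration to surgery | none | 0 to 28 days |
| Surgery after SEMS | day 0 to 14 | day 28 (0+28+0) to day 70 (14+28+28) |
| Neoadjuvant chemotherapy | no | yes |

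The planned windows do not overlap, and neither schedule covers days 15 to 27. In a between-arm model with an intercept, a delay term and a chemotherapy term, the last two columns are identical. The rank is 2 for 3 parameters, so the two effects cannot be estimated separately.

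**3. What a hazard ratio near 1 would mean.** Write the arm hazard ratio as (delay effect) × (chemotherapy effect). With exponential survival, the hazard ratio implied by two survival rates at the same time is ln(S_delayed)/ln(S_early). Sample size and randomization gives two pairs of rates:

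- Planning rates, 80% and 40%: ln(0.40)/ln(0.80) = 4.11. A chemotherapy hazard ratio of 1/4.11 = 0.24 would cancel this.
- Retrospective 5-year rates, 84.1% for control and 37.5% for surgery at 4 weeks without neoadjuvant chemotherapy: ln(0.375)/ln(0.841) = 5.66. A chemotherapy hazard ratio of 1/5.66 = 0.18 would cancel this.

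So 4.11 × 0.24, 5.66 × 0.18 and 1.00 × 1.00 all give an arm hazard ratio of about 1, and the trial would see the same result in each case.

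**4. Could two windows give an optimum?** Even if chemotherapy were equal in both arms, the comparison would show only which of two windows did better. It would not locate a best interval.

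**The case against.** The strongest reply is that no planned inference rests on the interval aim. The endpoint, the sample size and the Cox test all concern two randomised strategies. The end of the Discussion also describes the trial as assessing the oncologic safety of neoadjuvant chemotherapy after stenting. On this view the defect is only one of wording. Much of that stands: the primary comparison is sound for the strategy question, and the remedy is indeed wording. But the interval aim appears in three places, comes first in the Introduction, and is joined in the Discussion to a stated intention to analyse outcomes by interval. The wording therefore governs what the trial may claim.

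A second reply is that the interval also varies within each arm, and that the Discussion itself raises the question of surgery within 7 or 14 days. That is fair. Within-arm evidence is weak and non-randomised, but not worthless. It cannot compare early with late surgery free of chemotherapy.

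Some stronger readings are tempting, and the document does not support them:

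- *That the survival comparison suffers from immortal time.* The intention-to-treat comparison groups patients by assignment from a common origin, not by the interval achieved. The problem would arise only in an analysis grouped by achieved interval, and the statistical analysis section specifies none.
- *That the true delay hazard ratio is 5.7.* This comes from one pair of unadjusted retrospective rates, given without group sizes or confidence intervals, for surgery at 4 weeks rather than up to 10. The planning rates give 4.1, and the article itself treats so large a difference as unrealistic.
- *That leaving out a delayed arm without chemotherapy was an oversight.* The article's own retrospective figure of 37.5% is a reason to doubt that option.

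**Conclusion.** The point holds as a mismatch between objective and design. Within the randomised comparison, interval and neoadjuvant chemotherapy are completely aliased (day 0 to 14 without, about day 28 to 70 with), so no conclusion about the optimal interval, or about the safety of delay alone, can come from it. The strategy comparison remains valid at its stated 80.1% power.

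The aliasing follows from the two schedules as written and needs no survival assumption. The hazard ratios of 4.1 and 5.7 assume exponential survival and are illustrations only; the conclusion does not depend on their size. Departures from schedule could produce some overlap in achieved intervals, but those patients would be self-selected and would not restore a randomised contrast.

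**What to change.** - In the Abstract, Introduction and Discussion, restate the objective and planned conclusions as non-inferiority in overall survival of neoadjuvant FOLFOX followed by surgery versus surgery within two weeks of SEMS placement. Remove the references to an optimal time interval.
- State that a non-inferior result applies to the whole strategy and does not show that delay without chemotherapy is safe.
- Label any analysis by interval as exploratory, non-randomised and within-arm, never pooled across arms.
- For any such analysis timed from surgery, say that it is conditional on reaching resection. In the experimental arm, surgery follows only if restaging shows no metastases. If the clock stays at SEMS placement, grouping by achieved interval needs a landmark or time-dependent method to avoid immortal time.

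The cost is a change of wording and the loss of a claim that the trial could not support. Arms, sample size, power and data collection stay as they are.

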## Methods and design

### Patient enrollment

This study was designed as a multicenter, prospective, non-inferiority, randomized, controlled comparative study. The study will last approximately six years, consisting of three years of inclusion and three years of follow-up. Patients will be enrolled at eight University hospitals affiliated with The Catholic University of Korea, including Seoul St. Mary’s Hospital, Yeouido St. Mary’s Hospital, Uijeongbu St. Mary’s Hospital, St. Vincent’s Hospital, Incheon St. Mary’s Hospital, Eunpyeong St. Mary’s Hospital, Bucheon St. Mary’s Hospital, and Daejeon St. Mary’s Hospital. Complete information will be provided to patients and their guardians after the successful placement of SEMS for obstructive lesions on the left side of the colon. Informed consent will be obtained from the patients after pathologic confirmation of adenocarcinoma and completion of preoperative staging work-up.

Consecutive adult patients between the ages of 20 and 75 with pathologically confirmed adenocarcinoma will be eligible if they meet the following criteria: clinical stage II or III colon cancer with colonic obstruction; a colon cancer located between the splenic flexure colon and rectosigmoid junction colon, defined as a tumor located above 15 cm from the anal verge; no colonic injury and successful decompression of the colon within 48 h after SEMS placement; Eastern Cooperative Oncology Group (ECOG) performance status of 0–2; American Society of Anesthesiologists (ASA) physical status grade I, II, or III; and a negative urine human chorionic gonadotropin (hCG) test in women who are in their fertile period.

Patients will be excluded from the study if there is any suspicion of distant metastasis or the presence of another primary malignant lesion. Additionally, patients with a clinical stage of T1 or T2 and N0 will be excluded if they exhibit signs of perforation or severe ischemia that necessitates emergency surgery. Other exclusion criteria include complications related to the placement of self-expanding metal stents (SEMS), such as infection, severe bleeding, or perforation following SEMS placement, as well as colonic obstruction caused by benign strictures.

### Ethics

We have already obtained approval from the review board of The Catholic University of Korea, CMC Clinical Research Coordination Center (XC21MIDI0004). The patients will be enrolled in the study, and their clinical information will be collected using a predetermined dataset. The informed consent will be obtained after confirming the successful placement of SEMS, in accordance with the guidelines and regulations for our institution’s prospective randomized controlled study. The review board will handle adverse events, and researchers will report any related to the study protocol. This study has also been registered on ClinicalTrials.gov with the identifier NCT04889820. This is version 1.0 for this study.

### Definition

In this study, left-sided obstructive colon cancer will be defined as a confirmed obstructive lesion caused by adenocarcinoma, which arises from the splenic flexure colon to the rectosigmoid colon. Obstructive colon cancer will be diagnosed when patients complain of symptoms such as abdominal pain, distension, and the absence of stool and flatus passage. Radiologic findings from an abdomen and pelvic computed tomography (CT) may reveal severe dilation of the proximal colon due to a suspicious obstructive lesion. Patients exhibiting any signs of generalized peritonitis due to colonic perforation will be excluded from the study on obstructive colon cancer.

### SEMS insertion and preoperative preparation

In patients with abdominal pain and distension, we will initially conduct a plain X-ray. If colon obstruction is suspected, we will then proceed with an abdominopelvic CT scan. If radiologists suspect obstruction from colon cancer, we will explain to the patient and their guardians the need and risks associated with colonoscopic biopsy and stent placement. Once informed consent is obtained, all SEMS procedures will be performed by experienced gastroenterologists within 48 h of the initial hospital visit at each hospital that is equipped with SEMS. The SEMS will be inserted by a gastroenterologist with the aid of colonoscopic and/or fluoroscopic guidance at all hospitals. The HANARO stent (M.I. Tech Co., Ltd, Seoul, South Korea) or the Niti-S stent (Taewoong Medical, Co., Ltd, Gyeonggido, South Korea) will be used in all cases. After successfully inserting the SEMS, complications, expansion of the SEMS, and resolution of the intestinal obstruction will be monitored through serial plain abdominal films. Patients will undergo chest CT or positron emission tomography-CT (PET-CT) scans, and serum carcinoembryonic antigen (CEA) levels will be obtained after confirmation of adenocarcinoma through colonoscopic biopsy. Additionally, a colonoscopy will be performed after mechanical bowel preparation to identify any other colonic neoplasms once the SEMS has fully expanded and the patient’s abdominal symptoms have disappeared. Before randomization, a full colonoscopic evaluation will be performed to identify any lesions in the proximal colon. If there is no colon cancer in the proximal region, patients will be eligible to participate in this study. However, when a full colonoscopic evaluation is difficult to perform for various reasons, evaluating the proximal colon through PET-CT can be considered as an alternative option. All patients will receive perioperative intravenous antibiotics, and mechanical bowel preparation will be performed prior to surgery. After obtaining informed consent, the patients will be enrolled and randomly assigned to either the control group or the experimental group.

